### 2.9. Primary Outcomes

#### 2.9.1. Fundamental Motor Skills (FMSs)

These will be assessed by means of the test of gross motor development-second edition (TGMD-2) [24]. This battery measures 12 FMSs in two different domains (locomotor skills and object control). The locomotor skills domain contains 6 assessments: (i) running, (ii) galloping, (iii) hopping on one foot, (iv) long jumping, (v) horizontal jumping and (vi) lateral sliding. The object control domain also includes 6 assessments: (i) batting a stationary ball, (ii) stationary dribbling, (iii) catching a ball, (iv) kicking a ball, (v) throwing a ball and (vi) rolling a ball. Estimated administration time is ≤10 min per child. The 6 locomotion skills and 6 object control skills incorporate 24 criteria, allowing a total score from 0 to 48 points. The domain scores can be transformed into a standard score (median = 10.0 and standard deviation = 3.0) and subsequently into a gross motor quotient (median = 100.0 and standard deviation = 15.0). This information can be found in percentiles that allow the child to be placed in normative values with respect to a reference population. The original TGMD-2 reports high test–retest and inter-rater reliability (all r values > 0.85), as well as good internal consistency that varies between 0.85 and 0.88 for each ability [24]. In addition, its content, construct and concurrent validity have been demonstrated in children aged ≥ 3 years in countries such as Chile [25,26], Brazil [27] and Korea [28]. 

#### 2.9.2. Language Development

The language test for preschoolers (TELEPRE) [29] will be used. The purpose of this assessment is to measure the language of children in initial educational levels (3 to 6 years old) by means of 4 domains: (i) language comprehension, (ii) language expression, (iii) vocabulary and (iv) language description. The administration of the instrument requires a booklet of questions, various objects (bottle, toy car, pencil, plate, needle, cup, paintbrush, screw, sponge, small ball, button, small book, spoon, scissors, matchbox; plus three objects that serve as distractors) and 3 pictures representative of situations (i.e., serving milk to a cat, setting the table and being in a toy store) to be described by the child. To administer the instrument, a room free from noise or other distraction is required, in which the evaluator, the child and a classroom assistant will be present. The estimated application time is ≤25 min. The test scores vary according to the domain and age of the child being evaluated; they are described in detail below, according to the original manual [29]. To interpret the scores, the original manual [29] proposes the use of T-scores (average = 50 points and standard deviation = 10). Regarding the validation of the instrument, its internal consistency varies between 0.87 and 0.93, according to the domain analyzed and a concurrent validity with the test of psychomotor development (TEPSI) [29].

#### 2.9.3. Physical Activity Level

This will be objectively monitored by accelerometers (ActiGraph GT9X, Pensacola, FL, USA). The device will be worn at the waist on an elastic belt, at the mid-axillary line on the right side. Children will be instructed to wear the accelerometer 24 h a day, for at least 7 days, including 2 weekend days, and only to remove the device when bathing or engaging in water activities [30]. The minimum amount of data considered acceptable for analysis purposes will be five days (including one weekend day) [30], with at least 10 h/day of wear time. LPA, MVPA and SB, following the cut-off points proposed by Lettink et al. [31], will be considered for analysis. Sleep time will not be taken into account. Data will be verified using Actilife software version 5.6 (ActiGraph, Pensacola, FL, USA). Consecutive 20 min blocks of 0 count will be considered as non-use of the device and discarded from the analyses. Data will be collected at a sampling rate of 30 Hz, downloaded in one-second periods, and aggregated over 15-s periods [32]. 

### 2.10. Secondary Outcomes

#### 2.10.1. Morphological Variables

Bipedal height will be measured by placing a tape measure (Bodymeter 206, SECA, Hamburg, Germany; accuracy of 0.1 cm) on the wall and utilizing the Frankfort plane in a horizontal position. The body weight will be determined using an electronic scale (Tanita BC-730 Tokyo, Japan; accuracy of 0.1 kg) and the body mass index will be computed by dividing the body weight by the square of the bipedal height (kg/m^2^). Waist circumference and bicep circumference will be measured using an inextensible tape measure (Seca-201, Hamburg, Germany) with an accuracy of 0.1 cm. Similarly, skinfolds (mm) will be measured in the bicipital, tricipital, subscapular and suprailiac regions using a plicometer (Harpenden-FG1056, England; accuracy of 0.2 mm) that exerts a constant pressure of 10 g/mm^2^. These variables will be assessed by an anthropometrist, level II, certified by the International Society for the Advancement of Kinanthropometry (ISAK) [33]. Measurements will be taken during the morning of a fasting day in a conditioned room.

#### 2.10.2. Sociodemographic Variables

A questionnaire integrating items proposed in previous studies [34] will be used for this measure. Legal guardians will be asked to respond to the following: (i) child’s name; (ii) child’s date of birth; (iii) in which country was the child born; (iv) in which country I was born; (v) what is my relationship to the child; (vi) marital status of the parents or guardians; (vii) in what area does the child reside; (viii) does the place where the child lives have a yard; (ix) how many people live with the child; (x) how many persons work in your household; (xi) what is the total family income of the people living with the child (approximately); (xii) what is the highest level of schooling you have. 

### 2.11. Statistical Analysis

R statistical software, version 4.1.2, will be used [35]. Descriptive statistics will be generated where the summary and dispersion measures of the data will be calculated. The variables will be subjected to the Shapiro–Wilk test for normality and Levene’s test for homogeneity of variance.

### 2.12. Intention-to-Treat Analysis

A two-factor repeated measures ANOVA will be used to determine the effects of the intervention on the outcomes (group × time). Post hoc tests will be performed with an alpha adjusted by Bonferroni to identify statistically significant differences. The effect sizes will be calculated utilizing Cohen’s d [36] within the group and between the groups, using the following equation: effect size = (post-mean − pre-mean)/standard deviation combined. The level of significance will be set at 5%. The intraclass correlation coefficient will be used to verify the measurement’s reliability, with a predetermined threshold of 0.80 being used to include the data in the analyses. Furthermore, logistic regression will be performed to identify the association of the physical activity level with FMSs, language development and morphological and sociodemographic variable factors. For all statistical analyses, the sociodemographic variables will be considered as moderators (covariates). 

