## 2. Material and Methods

### 2.1. Study Design

The study is based on a double-blind, repeated measures and parallel groups (6 interventions and 6 controls) (randomized controlled trial) experimental design; considering previous studies, a quantitative approach will be adopted [16]. The methodology followed will be the Consolidated Standards of Reporting Trials Statement (CONSORT) methodology [17]. 

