### 2.3. Sample Size Calculation

Twelve children will be recruited from each class group (without gender distinction). The distribution of the class groups (12 class groups) will be in 3 experimental groups (6 class groups, n ± 72 children) and 3 control groups (6 class groups, n ± 72 children). The distribution by clusters or strata is justified by the fact that the use of individual randomization would imply a high probability of contaminating the control groups since it is unfeasible to prohibit children from interacting in school classrooms or recreational spaces (i.e., playgrounds, hallways, laboratories), which is where the study intervention will be carried out [18,19]. In addition, in the Maule region (one of the sixteen regions into which to Chile is divided; located in the center of the country and bordered to the north by the O’Higgins region, to the east by the provinces of Mendoza and Neuquén belonging to Argentina, to the south by the Ñuble region and to the west by the Pacific Ocean), there are 54 educational establishments that provide preschool education with an enrollment of approximately 1080 children. 

The sample size calculation indicates that the ideal number of participants per group is 10. As agreed in a previous study by Eyre et al. [15], we will use a mean difference of 3.22 total score of locomotor skill domains for this calculation as the minimum difference necessary for substantial clinical relevance, with a standard deviation of 0.70 points, considering an alpha level of 0.05 with a power of 80% and an expected loss of 15%. The GPower program (version 3.1.9.6, Franz Faul, Universiät Kiel, Kiel, Germany) will be used to calculate the statistical power. 

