### 2.4. Randomization and Blinding

The 12 class groups will be selected from 4 upper-middle-level classes (2 experimental and 2 control; age range between 3 and 4 years), 4 transition level 1 classes (2 experimental and 2 control; age range between 4 and 5 years) and 4 transition level 2 classes (2 experimental and 2 control; age range between 5 and 6 years), which will be randomized with stratified sampling [16]. This consists of segmenting the classes that agree to participate in the study according to educational levels (strata) and then performing a random sampling on each of them, using R statistical software, version 4.1.2. This study is considered double-blind because the measurements will be performed by professionals who are external to the research. 

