### 2.8. Outcomes and Procedures

The first meeting will be to obtain the agreement of the educational establishments and educators, to obtain the necessary signatures of informed consent and to explain the scope and aim of the study; also, the children will be randomly assigned to the intervention groups. During the following 2 weeks, the first assessments (pre-tests) will be carried out, before the 12-week CMSI is implemented; finally, the second assessments (post-tests) will be administered. One of the researchers will supervise all of the assessments and CMSI, and there will be a predefined order that will be followed by expert personnel in the assessments: (i) FMSs (physical education teacher specializing in early childhood care); (ii) language development (kindergarten teacher); (iii) physical activity level (physical education teacher); (iv) morphological variables (anthropometrist); and (v) sociodemographic variables (kindergarten teacher and physical education teacher). Figure 2 shows a summary of the assessments and sessions that are usually part of CMSI.

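### Class groups are allocated, but the effect is tested on children with a group × time ANOVA that has no class term, so the 5% level is not held if changes correlate within class

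*Protocol article*

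**What the plan says.** **Unit of allocation.** Section 2.1 describes "parallel groups (6 interventions and 6 controls"). Section 2.3 sets the class size: "Twelve children will be recruited from each class group". It defends the design as a guard against contamination of the control classes: "The distribution by clusters or strata is justified by the fact that the use of individual randomization would imply a high probability". Section 2.4 explains the stratified draw as "segmenting the classes that agree to participate in the study according to educational levels (strata"), followed by random sampling within each level, with two experimental and two control classes per level.

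**Analysis.** Section 2.12 fixes the test of effect: "A two-factor repeated measures ANOVA will be used to determine the effects of the intervention on the outcomes", with group × time as the two factors, at a 5% significance level. The only intraclass correlation it names is for measurement reliability, with a threshold of 0.80. The only covariates are the sociodemographic variables, and the guardian questionnaire in section 2.10.2 does not include class. Section 2.13 applies the same procedures to the per-protocol set.

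**A conflicting sentence.** Section 2.8 says "the children will be randomly assigned to the intervention groups".

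**The concern.** When classes are allocated, the evidence on the arm comparison comes from 12 classes, not from 144 separate children. By section 2.6 the intervention is given in sessions held in the children's usual classroom, so classmates share a setting and a delivery. Section 2.3 itself says that interaction between children cannot be prevented. Correlated changes within a class are therefore plausible.

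A child-level ANOVA reads variation between classes as if it were an arm effect. It could declare the intervention effective because a few experimental classes happened to progress well. The same test is applied to all the primary domains in section 2.9, and section 4 looks ahead to curriculum use if the result is favourable.

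**Working it through.** **Inputs from the document.** 6 classes per arm (2.1, 2.3); m = 12 children per class, so 72 per arm and 144 in total (2.3); three levels with 2 + 2 classes each (2.4); alpha 0.05 (2.12), taken as two-sided because sidedness is not stated.

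**Assumed input.** The ICC of the change score between classes within a level is not given. The range used is 0 to 0.20.

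**Step 1: what the ANOVA tests.** With two arms and two time points, the group × time F test equals the squared t test on the children's change scores. Its error degrees of freedom are 144 − 2 = 142. If group means the six level-by-arm groups shown in Figure 1, they are 144 − 6 = 138. A class-level analysis with arm and level has 12 − 1 (mean) − 1 (arm) − 2 (level) = 8.

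**Step 2: formulas.** Design effect DEFF = 1 + (m − 1) × ICC = 1 + 11 × ICC. Child-level standard errors are too small by a factor of about √DEFF. Approximate actual two-sided error = 2 × [1 − Φ(1.96/√DEFF)]. Worked at ICC 0.05: DEFF = 1.55, √1.55 = 1.245, 1.96/1.245 = 1.574, error = 11.5%.

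**Step 3: check by simulation.** 40,000 null trials per ICC, 6 vs 6 classes of 12, two-arm test on change:

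| ICC (assumed) | DEFF | Effective n per arm (72/DEFF) | Error, formula | Error, simulated |
|---|---|---|---|---|
| 0 | 1.00 | 72 | 5.0% | 4.9% |
| 0.01 | 1.11 | 65 | 6.3% | 6.2% |
| 0.02 | 1.22 | 59 | 7.6% | 7.6% |
| 0.05 | 1.55 | 46 | 11.5% | 11.5% |
| 0.10 | 2.10 | 34 | 17.6% | 17.8% |
| 0.20 | 3.20 | 22.5 | 27.3% | 27.7% |

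The row at ICC 0 reproduces the plan's nominal 5%. Under the six-group reading, with the arm contrast tested against the child-level error, the rates are the same or slightly higher. A t test on class means (10 df), and a class-mean regression on arm and level (8 df), both stay at about 5% throughout.

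**Step 4: role of stratification.** Variation between levels is balanced across arms by design and does not inflate the error. In simulation, if half of a total between-class share of 0.10 is due to level, the two-arm test rejects about 11%, close to the 0.05 row. If all of it is due to level, it rejects about 4%. The ICC in the table must therefore be read as within level.

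**Step 5: detectable difference at 80% power.** Treating children as independent: 0.47 SD of the change. With class means (10 df) it is 0.518 × √DEFF, which gives 0.55, 0.57, 0.65, 0.75 and 0.93 SD at ICC 0.01, 0.02, 0.05, 0.10 and 0.20. With 8 df it is slightly larger.

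**The case against.** **The article is condensed, and detail may sit in a fuller plan.** This would answer silence on clustering. But section 2.12 names the model and its two factors, and that model does not fit the allocation described in sections 2.3 and 2.4.

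**"Group" may mean six level-by-arm groups.** This is possible: the abstract and section 2.3 speak of three experimental and three control groups, and Figure 1 labels six. A reader might infer that educational level is missing from the model, but the text is ambiguous on that. Age may also enter through date of birth in the questionnaire. Neither possibility adds a class term, because each level-by-arm cell still holds two classes.

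**The size is unknown.** This stands. No ICC is given, at 0.01 to 0.02 the excess is modest, and at 0 there is none.

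**Section 2.8 speaks of children being assigned.** A reader might infer individual randomisation. Sections 2.3 and 2.4 give the detailed account, with reasons, and it is allocation of classes.

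**Stronger readings that the document does not support.**
- That each experimental class has its own educator: section 2.6 says only that trained early childhood educators deliver the sessions in the usual classroom. The shared classroom is enough for the concern.
- That the planned confidence intervals are wrong: section 2.12 plans none.
- That testing change is itself an error: under randomisation it is valid, and adjusting for the pre-test is a gain in efficiency.

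**Conclusion.** The point holds. The stated test ignores the unit of allocation in both the intention-to-treat and the per-protocol analysis, and nothing else in the document corrects for it. The nominal 5% is exceeded for any positive within-level between-class ICC of the change, always towards too many false positives. The actual rate is about 6%, 8%, 11%, 18% and 28% at assumed ICCs of 0.01, 0.02, 0.05, 0.10 and 0.20.

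These figures rest on equal classes of 12, a two-sided test and normally distributed changes; the ICC range is an assumption and not a figure from the document. Any 95% interval later taken from this model would be too narrow, covering about 94%, 92%, 88%, 82% and 72% at the same ICCs. Because the main inference on every primary outcome is affected, this should be corrected before analysis.

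**What to change.** In section 2.12, and so in section 2.13, replace the ANOVA with one of these:

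- a linear mixed model for the post-test score with arm, the child's own pre-test score, educational level and a random intercept for class, using Kenward-Roger degrees of freedom; or
- an analysis of class means on arm and level, with about 8 degrees of freedom.

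If both time points are modelled jointly, include a class × time random effect. A class intercept alone cancels out of the change and leaves the group × time test uncorrected.

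A permutation test over the stratified allocations is an optional support. If two of four classes are drawn per level, there are C(4,2)³ = 6 × 6 × 6 = 216 allocations, so the smallest two-sided p is 2/216 = 0.009. That could not pass a Bonferroni threshold over nine primary measures (2 motor + 4 language + 3 activity; 0.05/9 = 0.0056), should one be adopted. Section 2.12 currently applies Bonferroni only to post hoc tests.

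Reconcile the sentence in section 2.8 with the class allocation in sections 2.3 and 2.4.

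**Cost.** The correction is to analysis wording and needs no new data. Intervals will be wider, and the detectable difference rises from 0.47 SD to roughly 0.55 to 0.93 SD over the assumed ICC range. The sponsor should weigh that against section 2.3, whose sample size calculation shows no allowance for clustering.

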### 2.7. Control Groups

The upper-middle-level control groups (n = 2 classes; n = 24 children), transition level 1 control groups (n = 2 classes; n = 24 children) and transition level 2 control groups (n = 2; n = 24 children) will participate in the assessments (initial and final) and will be asked to maintain their regular sessions at their educational establishments. At the end of the intervention period (according to the results obtained), the control group children, parents and/or legal guardians, managers and coordinators of each community will be contacted and provided with the material so that they can replicate the experience. In addition, the educators of these establishments (teachers and classroom assistants) will be trained in CMSI strategy.

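### The group × time test uses the pre-test inefficiently and does not name the stratification level as a model term, so the effect estimate is valid but less precise than it could be

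*Protocol article*

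**What the plan says.** Section 2.12 of the protocol article names one test for the intervention effect: "A two-factor repeated measures ANOVA will be used to determine the effects of the intervention on the outcomes", with group and time as the two factors. Section 2.13 repeats the same procedures for the per-protocol analysis.

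There are two measurement times. Section 2.8 says "the first assessments (pre-tests) will be carried out, before the 12-week CMSI is implemented", with the post-tests after the intervention. Section 2.7 says that the control children "will participate in the assessments (initial and final").

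Section 2.4 describes the randomisation as "segmenting the classes that agree to participate in the study according to educational levels (strata) and then performing a random sampling on each of them". There are three levels, each with two experimental and two control classes.

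On covariates, section 2.12 says only: "For all statistical analyses, the sociodemographic variables will be considered as moderators (covariates"). Section 2.10.2 lists these items. They include "ii) child’s date of birth", but neither the pre-test score nor the educational level.

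**The concern.** With two times, the group × time F test is identical to a t test on change scores. A change score subtracts the whole pre-test value, so it sets the baseline slope at 1 and does not estimate it. When the pre-post correlation is below 1 and the two variances are equal, the best slope is below 1, and the change score carries avoidable noise.

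A factor used to stratify randomisation would normally appear in the analysis. If it does not, any difference in growth between the 3-to-4, 4-to-5 and 5-to-6-year classes goes into the error term.

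Only 12 classes are randomised, so precision is scarce. The stake is power and the width of the confidence interval, not bias.

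**Working it through.** **The plan's own figures.** The article gives no pre-post correlation, no intraclass correlation (ICC) and no precision for this test. Its only sample-size result, 10 per group (section 2.3), involves no baseline adjustment. It is also not reproduced: 3.22/0.70 = 4.6 SD needs 3 per group by a two-sided t test at 80% power, and 4 after 15% loss. Nothing below depends on it.

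**Step 1: child level.** Let σ² be the common variance at pre-test and post-test, and ρ the pre-post correlation (assumed).

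- Change score: variance 2σ²(1−ρ).
- Post-test adjusted for pre-test: variance σ²(1−ρ²).
- Ratio: (1−ρ)(1+ρ) / [2(1−ρ)] = (1+ρ)/2.

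| ρ (assumed) | Adjusted | Change | Ratio | 144 × ratio |
|---|---|---|---|---|
| 0.3 | 0.91 | 1.40 | 0.65 | 94 |
| 0.5 | 0.75 | 1.00 | 0.75 | 108 |
| 0.7 | 0.51 | 0.60 | 0.85 | 122 |

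The last column is the number of children with whom the adjusted analysis matches the planned analysis of 144, ignoring clustering.

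**Step 2: the level term alone.** These are simulated mean model standard errors (SE) for the change score, with 12 classes of 12, ρ = 0.6 and no class effect.

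| Level effect | SE without level | SE with level |
|---|---|---|
| Constant over time | 0.149 | 0.149 |
| Growth differs by 0.3 SD per level | 0.155 | 0.149 |
| Growth differs by 0.5 SD per level | 0.164 | 0.149 |

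A constant level difference cancels in the change score. Omitting level matters only if growth differs by level. The reported SE is then too large, while the estimate's actual spread is unchanged, because level is balanced by design.

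**Step 3: the whole change, analysed by class.** Inputs:

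- 12 classes of 10 analysed children (12 less 15% is 10.2).
- A true effect of 0.45 SD, close to the standardised differences of 0.44 and 0.47 cited in the Introduction.
- Assumed ICC of 0.05 to 0.10 and assumed ρ of 0.5 to 0.7.

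The change-score test has 12 − 2 = 10 df. Adding two level terms leaves 8, and the critical t goes from 2.23 to 2.31. That cost is included below.

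| Setting | Power, change score | Power, adjusted for pre-test and level |
|---|---|---|
| Equal growth across levels | about 35–67% | 44–70% |
| Growth differs by 0.2 SD per level | about 30–54% | 43–71% |
| Class effects persist (class-level correlation 0.9, ICC 0.10), equal growth, ρ = 0.5 | 56% | 57% |
| The same, ρ = 0.7 | 73% | 73% |

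The largest gain is 71 − 54 = 17 points; the smallest is about 0. Both estimates were unbiased, and type I error was about 5% for both where it was checked (ICC 0.10, ρ = 0.5).

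**Step 4: what each part does.** Adding level alone to a change score costs 1 to 3 points of power when growth is equal, and gains 4 to 10 when it differs by 0.2 SD per level. The pre-test must enter as the child's own score. If the baseline slope is estimated from the 12 class means (7 df), power can fall: 53% to 50% at ICC 0.10 and 68% to 65% at ICC 0.05, both at ρ = 0.7.

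**The case against.** The strongest reply is that nothing here is stated wrongly. Group × time ANOVA on pre-post data is conventional and its estimate is unbiased under randomisation. Exact model terms are often left to an analysis plan. The first part stands. The second does not dispose of the point, because section 2.12 does fix a model, and that model is the less efficient one.

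A reader might infer that the plan ignores the baseline. It does not: the pre-test is the first time point, so chance baseline differences are subtracted.

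A reader might also infer that level is certainly left out. The text does not settle this. Date of birth is among the covariates and tracks level closely. Section 2.3 describes three experimental and three control groups, so group might have six levels. But the article states neither use, and a six-level group would leave no single arm contrast.

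The growth difference of 0.2 SD per level is an assumption. The Introduction says that motor competence rises with age, which supports level differences but not unequal growth over 12 weeks. Age-normed scores, available for both TGMD-2 and TELEPRE (sections 2.9.1 and 2.9.2), could shrink level differences further.

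Finally, the point overlaps with the missing class term, which is the larger problem in the same section. In the simulation with a class ICC of 0.10, the true SE of the change-score effect was 0.24 against a model SE of 0.156. Adjusting for baseline and level alone did not cure it (0.229 against 0.141). The two remain distinct: a random class effect added to the group × time model would still fix the baseline slope at 1.

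**Conclusion.** The concern holds as one of efficiency. The planned test holds the baseline slope at 1 and does not name the stratification factor. At child level the adjusted effect has 0.65 to 0.85 of the change-score variance for ρ from 0.3 to 0.7, given equal variances. By class, the power gain from the full change is about 0 to 17 points. It is near zero when class effects persist strongly and growth is equal across levels, and largest when growth differs by level. With the child's own pre-test as covariate, power did not fall in any setting examined.

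The direction is secure. The size is not, because ρ, the ICC, the class-level correlation and the growth differences are all assumed. It would go too far to say that the treatment effect is biased, or that precision is being given away at no price: the level term has a small cost in degrees of freedom.

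**What to change.** In section 2.12, replace the group × time test with a model of the post-test score on arm (two levels), the child's own pre-test score and educational level (three strata). Fit it within the class-clustered analysis, for example with a random effect for class, and with a small-sample correction to the degrees of freedom. Report the adjusted arm difference with its 95% CI as the treatment effect. Section 2.13 then follows by its existing cross-reference. Defining arm as two levels also removes the doubt about a six-level group.

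The cost is a change of wording and no new data. Two of the 10 class-level degrees of freedom go to level, which loses 1 to 3 points of power for that term alone if growth is equal across levels. The change complements the correction for clustering and does not replace it.
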